#### Sensitivity analyses

Sensitivity to population changes:

Analysis assessing the impact of the timing of the prophylactic antibiotic policy change, including comparison of analysis restricted to the years 2006–2010 (before the change in the NICE guideline) compared with years where over 50% of hospitals had introduced the policy.Analysis of the primary outcomes in the full HES dataset (including data for the hospitals that do not respond to the survey and therefore preclude us linking information about prophylactic antibiotic policy at hospital level) using the estimated probability of introduction of preincisional antibiotics according to calendar year, to investigate the consistency of findings.Analysis investigating the impact of the data recording quality (restricted to HES-linked records in THIN-CPRD database as the most accurate source of records for the mode of delivery).Exploratory sensitivity analysis employing the discordant sibling approach (restricting the analysis to women who gave birth by CS more than once during the study period including before and after the change in the prophylactic antibiotic policy compared with women who gave birth by VD more than once during the study period) to control further for family-related genetic and environmental factors.

Sensitivity to model changes:

Analysis exploring whether the results are robust to the inclusion of a random effect for hospital.

Subgroup analyses:

Exploratory subgroup analysis in HES mother-child linked database by prophylactic antibiotic type administered according to the individual hospital policies to investigate the potential impact of different antibiotics (cefuroxime alone, co-amoxiclav alone, cefuroxime+metronidazole) on child outcomes.Exploratory subgroup analysis by the type of CS (it is hypothesised that children delivered by elective CS have a higher likelihood of asthma and related outcomes and are more likely to be exposed to in-utero antibiotics for longer than children born to women having an emergency CS).

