### Exclusion criteria

Children with missing delivery information will be excluded. In case of multiple births (eg, twins), one of the children will be randomly selected for inclusion to ensure independence of observations.

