### Study outcomes

The primary outcomes for the study are the incidence of (1) asthma and (2) eczema. The main analysis for primary outcomes will be done separately in the primary care dataset and the secondary care (HES) dataset (the latter including only hospitals for which the year of antibiotic prescribing policy change is known).

Secondary outcomes are other allergic and allergy-related diseases, autoimmune diseases, infections and inflammation, other immune system-related conditions, neurodevelopmental conditions, less specific measures of child health, healthcare utilisation and maternal postpartum infectious morbidity (table 1).

**Table 1 T1:** The list of secondary outcomes

Outcome	Corresponding secondary objective	Datasets analysed	
		Primary care	Secondary care
*Health conditions and symptoms in children*	1.		
Other allergic and allergy-related conditions:	1.a		
Food allergy/intolerance		x	
Allergic rhinitis and conjunctivitis		x	
>1 allergy related disease (asthma, eczema, food allergy/intolerance, allergic rhinitis and conjunctivitis)		x	
Penicillin allergy*		x	
Anaphylaxis*		x	x
High risk of anaphylactic reaction (prescribing of automatic injection devices containing epinephrine)*		x	
Autoimmune diseases:	1.b		
Type 1 diabetes*		x	x
Coeliac disease*		x	x
Juvenile idiopathic arthritis*		x	x
Scleroderma/systemic sclerosis*†		x	x
Inflammatory myopathies*†		x	x
SLE*†		x	x
Autoimmune (idiopathic) ITP*		x	x
Juvenile pernicious (megaloblastic) anaemia*		x	x
Childhood vitiligo*†		x	
Infections and inflammation:	1 .c		
Neonatal sepsis (early and late onset)			x
Other sepsis*			x
Wheeze		x	
Upper respiratory tract infections*		x	
Lower respiratory tract infections*		x	x
Bronchiolitis*		x	x
Gastroenteritis*		x	x
Inflammatory bowel disease†		x	x
Urinary tract infections*		x	x
Antibiotic prescribing*		x	
Other immune system-related conditions:	1.d		
Necrotising enterocolitis			x
Leukaemia*†		x	x
Neurodevelopmental conditions:	1.e		
Cerebral palsy		x	
Autism spectrum disorder*		x	
ADHD*		x	
Less specific measures of child health:	1 .f		
Colic*		x	
Failure to thrive*		x	
*Healthcare utilisation in children*	2.		
Primary care consultations*		x	
Hospital admissions*			x
*Maternal outcomes (6 weeks post partum)*	3.		
Composite infectious morbidity (wound infection, endometritis/endomyometritis, pelvic abscess, maternal sepsis, death attributed to infection)		x	x
Endometritis/endomyometritis		x	x
Wound infection		x	x

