We have a proposed linkage strategy which has already been validated by another recent study using matching algorithms based on HES data using organisation codes, admission dates, birth dates, general practice codes, sex, gestation and maternal age plus a number of other variables common to birth and maternity records. The database remains nationally representative for the main birth characteristics (such as gestational age, birth weight, sex and maternal age).^27^ The final output of this process will be a linked HES data set in which details of birth events and subsequent admissions of the children associated with these events can be elucidated.

HES alone, however, cannot be used to identify timing of prophylactic antibiotic administration and prophylactic antibiotics given. We will obtain the time point after which preincision antibiotic policy was introduced in each hospital from a national survey of maternity care providers in the UK. All maternity units undertaking CSs were included in the survey with a target response rate of 85%.

The exposure and outcome measures in the healthcare databases will be defined using the Read clinical code classification system used in primary care, and International Statistical Classification of Diseases and Related Health Problems 10th Revision (ICD-10) used for clinical diagnoses, the Office of Population Censuses and Surveys Classification of Surgical Operations and Procedures 4th revision (OPCS) for procedures and Healthcare Resource Groups (HRG) codes used in HES.

Recording of some variables in healthcare data, such as breastfeeding, is incomplete; we will therefore also investigate the trends in these variables by the mode of delivery using additional data sources such as the National Maternity Surveys.^28^

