### Methods

We will compare rates of diagnosis of asthma and other outcomes of interest over time in children born by CS, comparing outcomes according to whether each mother received preincisional antibiotics.

In the primary analysis, we will estimate a probability that each mother received preincisional antibiotics according to year of birth, based on national policy uptake rates in the year of delivery for primary care data. For secondary care data, we will use the response from each hospital indicating the year of local policy implementation.

The major threat to validity in this observational comparison is not from case-mix confounders (indications for and incidence of CS have changed little over the study period); rather they relate to temporal changes in diagnosis and in the recording of outcomes and other exposures which impact on the number of cases identified in routine data. Patterns of diagnosis of childhood asthma, for example, have changed over time, in part driven by the revisions in the national asthma management guideline and the potentially conflicting compliance and prevalence issues faced in meeting specific indicators of the Quality and Outcomes Framework (QOF) introduced in 2004.^29 30^

An analysis reliant on adjustment for confounding factors is unlikely to succeed in controlling for these changes as it is unclear (1) what all the drivers of all these changes have been, (2) whether any covariates exist which accurately describe these changes without substantial missing data and (3) challenges in specification of a functional form for the relationship between these covariates and outcome.

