### Analysis

The primary and secondary outcomes will be analysed using a Poisson regression model to estimate the relative risk of developing each outcome with preincision compared with postcord clamping antibiotics. We will assess for overdispersion and if high, consider other models, such as a negative binomial. Appropriate considerations will be made to allow for the autocorrelation of data. We will look at the autocorrelation and partial autocorrelation plots to ensure any autocorrelation is accounted for. An adjustment for calendar time will be included in the model to allow for season effects. We will include terms for year, age and the interaction between them and mode of delivery (CS or vaginal). The key outcome parameter will be estimated by an additional term to identify those who receive preincision rather than postcord clamping antibiotics.

Rather than being described in dichotomous form, we will estimate the probability of preincision antibiotics using data from the national survey and known hospital policy. The estimated coefficient will provide an estimate of the change in policy, adjusting for misclassification.

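### The main HES model assigns exposure by hospital but has no hospital term, so differences between early- and late-adopting hospitals can confound it and its intervals can be too narrow

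*Protocol article*

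**What the plan says.** All references are to the protocol article.

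- **Exposure (Methods).** "For secondary care data, we will use the response from each hospital indicating the year of local policy implementation". Primary care data instead use national uptake in the year of delivery.
- **Population (Study outcomes).** The HES main analysis is restricted, "the latter including only hospitals for which the year of antibiotic prescribing policy change is known". The policy years come from a national survey (Data sources) with a target response of 85%.
- **Model (Analysis).** Poisson regression: "We will include terms for year, age and the interaction between them and mode of delivery (CS or vaginal"), and then "The key outcome parameter will be estimated by an additional term to identify those who receive preincision rather than postcord clamping antibiotics". No hospital term is listed.
- **Variance (Analysis).** "We will assess for overdispersion and if high, consider other models, such as a negative binomial". Autocorrelation over time is also to be examined.
- **Hospital effect (Sensitivity analyses, model changes).** "Analysis exploring whether the results are robust to the inclusion of a random effect for hospital".

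The article therefore states a choice: the hospital effect is secondary, and the main HES model goes without it.

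**The concern.** The hospital is the unit that switches from unexposed to exposed. In the years when some hospitals have switched and others have not, exposed and unexposed CS children were born in different hospitals.

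The vaginal-birth group is the study's main defence, and it is built to remove temporal change that both delivery modes share. It cannot remove differences between hospitals. Vaginal births have exposure zero in every hospital and year, and without a hospital term the model does not know which vaginal and CS births share a hospital.

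Two things are at stake in a main analysis of a primary outcome. If adoption timing is related to a hospital's baseline asthma admission rate, that relation enters the estimated rate ratio. Even if it is not, ordinary between-hospital variation adds error that a Poisson standard error does not count.

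**Working it through.** **Inputs from the article.** HES person-years are 8 661 832 (CS) and 25 339 526 (vaginal), with 60 240 events in total (Table 2). The working adoption pattern is 0.2, 0.4, 0.6, 0.8 and 1 in 2010 to 2014. The stated HES targets are a rate ratio (RR) of 1.10 (over 80% power) and 1.12 (90%).

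**Assumptions, because the article gives no figure.** 150 equal hospitals (100 and 200 also tried); 20% adopting in each of 2010-2014; between-hospital SD of the log rate 0.1, 0.2 or 0.3; earliest-to-latest adopter rate ratio 1.1 or 1.2, graded evenly; year taken as birth year.

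**The plan's own power figure.** It was not reproduced. At RR 1.10, calendar-year exposure gives 97-99% power with no year-by-mode term and 19-34% with a linear one. The year-age rates and exact model form are not given, so this does not show an error, and nothing below relies on it. As described, that simulation drew exposure from yearly probabilities and has no hospital variation.

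**Step 1: confounding, by hand.** Take year-by-mode as categorical, so that only within-year contrasts among CS births inform the exposure term. Number the adopter groups g = 0 (2010) to 4 (2014). In year 2010 + t, with t = 0 to 3, groups 0..t are exposed (mean index t/2) and groups t+1..4 are unexposed (mean index (t+5)/2). The difference is 2.5 steps in every year. A gap R between the first and last groups is ln(R)/4 per step, so

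spurious log RR = 2.5 × ln(R)/4 = 0.625 ln(R).

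- R = 1.1: 0.625 × 0.0953 = 0.0596, RR 1.06
- R = 1.2: 0.625 × 0.1823 = 0.1140, RR 1.12

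Simulation with no true effect (300 runs per setting, 85% of HES person-years) gave 1.06 and 1.12. With a linear year-by-mode term it gave 1.05 and 1.10. If early adopters have the lower rates, the null RR is 0.94-0.95 or 0.88-0.90. With hospital fixed effects it was 1.00.

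**Step 2: interval width, by hand.** Weighting the four informative years by p(1-p) gives 0.2, 0.3, 0.3 and 0.2. The weights on the five group means are then 0.5, 0.25, 0, -0.25 and -0.5, whose squares sum to 0.625. With 30 hospitals per group, hospital variation adds variance 0.625 × SD²/30. The simulated Poisson standard error is about 0.029. Type I error is 2[1 - Φ(1.96 × 0.029/actual SE)].

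| Hospital SD | Added SD | Actual SE | Type I error |
|---|---|---|---|
| 0.1 | 0.014 | 0.032 | 8% |
| 0.2 | 0.029 | 0.041 | 16% |
| 0.3 | 0.043 | 0.052 | 28% |

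Simulated type I error across model forms was about 7-9%, 10-19% and 25-32%. The top of the last range also includes hospital-by-mode and hospital-by-year variation. At SD 0.2, coverage of the nominal 95% interval was 74% with 100 hospitals and 84% with 200. Monte Carlo error is about 2 percentage points at 300 runs.

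**Step 3: what the overdispersion step repairs.** Pearson scaling on hospital-by-year-by-mode cells gave coverage of 93%, 90% and 87% at SD 0.1, 0.2 and 0.3 (linear year-by-mode). Overall, type I error after scaling was about 5-13%, with one setting at 15% (SD 0.3, categorical year-by-mode). Scaling leaves the point estimate alone: with a 20% gap, SD 0.2 and categorical year-by-mode, coverage was 11% unscaled and 14% scaled.

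**Step 4: precision with hospital effects.** At a true RR of 1.10 (linear year-by-mode), power with hospital fixed effects was 92-98%. With cluster-robust standard errors but no hospital term it was 72% at SD 0.2 and 48% at SD 0.3.

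**The case against.** **The harm is conditional.** A reader might infer that adopter differences do confound the result. The article does not support that. It gives no hospital count, between-hospital variance or adopter characteristics, and nothing in it links adoption timing to baseline rates. The direction is unknown too. This stands: the model can be confounded; it is not shown to be.

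**The bias need not match the target effect.** A 10% gap gives about half of the 10% increase that HES is meant to detect. Only a gap near 20%, graded across adoption years, reaches it. This stands.

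**Intervals are not left unguarded.** A reader might take the unscaled error rates as the plan's actual performance. The overdispersion step repairs much of the interval problem, and an article need not name its variance estimator. This stands for the intervals, not for the confounding.

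**Other planned analyses would help expose the bias.** The full-HES sensitivity analysis uses calendar-year probabilities, which do not vary between hospitals within a year. The planned random effect would itself absorb most hospital differences. With 60 240/150 = about 402 events per hospital, shrinkage 1/(1 + 402 × SD²) is about 6% at SD 0.2 and 20% at SD 0.1. These are real checks. They still leave the headline with the weaker model, and the article does not say which result would prevail if they disagreed.

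**The point does not carry over to primary care.** Exposure there follows calendar year, not practice, so the early-versus-late-adopter mechanism is absent.

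**Conclusion.** The point holds for the HES main analysis. Exposure is set by hospital, the listed model has no hospital term, and the hospital effect is expressly secondary. The vaginal-birth group cannot remove hospital differences from this model.

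The mechanism follows from the text; the sizes do not. They rest on 150 equal hospitals, even adoption over 2010-2014 and the stated ranges of SD and adopter gap. On those terms, the possible bias runs from about half the target effect to all of it, and type I error after overdispersion scaling runs from near nominal to about 13%. If adoption timing is unrelated to baseline rates, only the interval problem remains.

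The documents do not support saying that the HES result will be biased, or that its intervals will certainly be too narrow. They do support saying that the main and sensitivity models are the wrong way round for an exposure assigned by hospital.

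**What to change.** Make the main HES model one with hospital fixed effects, allowing for hospital-by-mode differences, and with hospital-cluster-robust standard errors. Move the model without hospital effects to the sensitivity analyses. A random effect alone is the weaker choice because it assumes hospital effects are unrelated to adoption timing, which is the relation in question. Keep the full-HES calendar-year analysis as a check.

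The cost is analysis wording and computing time; no new data are needed. Intervals may be wider than unscaled Poisson ones.

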### Patient and public involvement (PPI)

We have involved the public throughout the development of this study. This has reconfirmed the importance of the research question, particularly: the importance of assuring the baby’s health as a main priority when deciding on delivery options; that uncertainty as to whether antibiotics given around the time of birth have an impact on children later in life should be resolved; that a robust study design is required to ensure the validity of the findings; a broad scope of important health and other outcomes which need to be considered; that the project needs to clearly communicate findings in terms of risks and benefits; that the findings regarding prophylactic antibiotics for CS should form part of the wider discussion regarding risks and benefits of medications in pregnancy.

Two lay parent representatives are members of our Project Management Group and an independent parent representative is a member of the Project Steering Group. We also held two PPI discussion groups with mothers and mothers-to-be in two different locations in the West Midlands. These women were from a range of backgrounds, including women from black and minority ethnic communities, a group often under-represented in research. The focus of the sessions was on exploring what women wanted to know about this research and particularly which health conditions in relation to this study were important to them. PPI helped us to confirm that we should look at a wide range of outcomes and also consider the severity of outcomes. In addition, a wider public consultation took place via a survey, a link to which was sent to the Royal College of Obstetricians & Gynaecologists (RCOG) Women’s Voices Involvement Panel and British Intrapartum Care Society (BICS) which includes lay members. Based on findings from the PPI workshops and the survey, we have added neurodevelopmental conditions as secondary/exploratory study outcomes.

Clear communication and publicising of key findings and messages are priorities of the study. Another PPI workshop is planned towards the end of the project to coproduce messages for dissemination via clinical networks, patient organisations and the media.

## Ethics and dissemination

Ethical approval for this study has been provided by the Ethical Review Committee of the University of Birmingham (ERN_17–1675). The THIN database was approved by the NHS South-East Multi-Centre Research Ethics Committee.^36^ Approval for the use of THIN and HES-linked data in this study was provided by the Independent Scientific Ethical Advisory Committee—Scientific Review Committee panel of the data provider, IQVIA (18THIN047). The CPRD has ethics approval for observational research using anonymised data from a National Research Ethics Committee.^37^ The use of CPRD for this study has been approved by the Independent Scientific Advisory Committee for MHRA Database Research (18_181AR2). The use of the HES database is exempt from NHS Research Ethics Committee approval because it involves the analysis of an existing dataset of non-identifiable data. Approval for the use of HES data was obtained as part of the standard NHS Digital data approval process.^38^ Health Research Authority (HRA) have confirmed that as the study involves linking anonymised patient data from established databases for our study only, HRA approval is not required.

The main aim of dissemination for this project is to ensure that parents-to-be and clinicians have clear information about the benefits and risks of preincision prophylactic antibiotics for CS based on the latest evidence to facilitate shared decision making. We will engage with the clinical and lay stakeholders throughout the project to benefit from the wider stakeholder input, to maximise the dissemination opportunities and to ensure that the research findings are communicated as widely as possible.

This will be achieved by: organising a further PPI workshop to produce a lay summary of the findings for wider dissemination, a dissemination event at the end of the project with lay, clinical stakeholders and professional organisations; dissemination to the clinical directors of maternity units; conference presentations, peer reviewed publications and dissemination via website and social media.

We will also maximise dissemination through: the Collaborations for Leadership in Applied Health Research and Care (CLAHRC) West Midlands (and its successor Applied Research Collaboration ARC) making use of their platform for dissemination; our strategic alliance, Birmingham Health Partners (BHP), which aligns three NHS trusts in the West Midlands area; the West Midlands Academic Health Science Network (AHSN) whose responsibility it is to adopt, diffuse and disseminate innovation in the NHS.
